# A randomized controlled trial for evaluating pain response in patients with spinal metastases following local versus whole vertebral radiotherapy: study protocol for phase II clinical trial

**DOI:** 10.1186/s12883-022-02746-7

**Published:** 2022-06-20

**Keywords:** Vertebral metastasis, Radiotherapy, Pain control

## Abstract

**Background:**

Patients with bone metastasis often experience severe pain that is difficult to control and seriously affects quality of life. Radiotherapy is an effective way to relieve pain in these patients. Currently, there is no standard recommended range of radiotherapy targets for vertebral metastasis. The effect of radiotherapy on pain relief varies among patients, and some patients with metastases have serious side effects.

**Methods:**

This study aims to verify whether reducing the radiotherapy range for vertebral metastases can achieve the same effect as whole vertebral radiotherapy while minimizing side effects. Sixty-six patients with pain caused by vertebral metastasis were randomly divided into two groups. The study group is receiving partial vertebrae body radiotherapy at the regions of abnormal signal, suspected invasion, and adjacent subclinical focus of vertebral metastasis, and the control group is receiving the same dose of radiotherapy on whole vertebrae body where metastasis occurred. After radiotherapy, along-term follow-up of patients will determine pain relief and side effects.

**Discussion:**

The expected results of this study are that local irradiation of vertebral metastases can achieve a palliative effect of pain control not less than total vertebral irradiation with fewer side effects.

**Trial registration:**

This study was registered in the Chinese Clinical Trial Registry (No: ChiCTR1900023401).

## Background

Patients with bone metastasis often present with severe pain that is difficult to control. The ASTRO guideline and its update recommend palliative analgesic radiotherapy for bone metastases [1, 2]. However, the effects of pain control therapies vary from one patient to another. In the past, the target setting of two-dimensional radiotherapy and 3D-CRT included the whole diseased vertebral body to treat spinal metastases, despite some patients suffering from pathological fracture, spinal cord compression, and other side effects of an excessive dose or range of vertebral irradiation.

The ISRC proposed dividing vertebral body into six parts in the target setting of spinal stereotactic radiosurgery, as shown in Fig. 1. As reported by a prospective study [3], there is a need to expand the CTV in SBRT for include adjacent physiologically occurring bone marrow spaces, which may have subclinical diseases and may become local recurrent lesions. The ISRC consensus guidelines on the target volume of spinal SRS suggest that CTV should include bone marrow signals suspected of microscopic invasion and adjacent normal bone. If the spinous processes, lamina / bilateral pedicle and vertebral body are affected or there are extensive metastatic diseases around the epidural space, the circumferential TVs around the spinal cord should be used [4].

**Fig. 1 Fig1:**
[figure not shown]
The International Spine Radiosurgery Consortium proposed to divide each vertebral body into 6 sectors: Sector 1 represents the vertebral body, sector 2 represents the left pedicle, sector3 represents the left transverse process and lamina, sector 4represents the spinous process, sector 5 represents the right transverse process and lamina, and sector 6 represents the right pedicle

At present, there is a single-center phase II prospective cohort study comparing the effect on pain control of conventional radiotherapy and SBRT in patients with spinal metastasis. In both treatment groups, patients had a comparable decrease in pain and analgesic use in the 3 months following treatment [2, 5]. However, there have no randomized controlled trials comparing the effect of local irradiation and whole vertebral irradiation on pain control in IMRT [6]. Therefore, we designed a randomized controlled trial to evaluate if irradiation of local metastases in the vertebral body as well as whole vertebral body irradiation can effectively control pain. We also investigated if side effects such as twinkling bone pain, spinal cord radiation injury, vertebral compression fracture, and nerve root compression were reduced.

## Methods

This study was registered in the ChiCTR (No: ChiCTR1900023401). This is a multicenter, prospective, phase II randomized controlled clinical trial. Patients with solid tumors diagnosed pathologically at our hospital were collected. All patients had vertebral metastases and pain symptoms. Patients will be randomized into 2 groups: study group^’^s clinical target volume setting was according to the ISRC consensus guidelines that recommend the vertebral body be divided into six parts, which include the area of vertebral destruction and adjacent parts, and control group’s clinical target volume include the whole vertebral body, The two groups of clinical target volume settings are shown in Fig. 2. Two groups will receive treatment with the same dose of 95% PTV DT 30 Gy/10 f IGRT (Image Guided Radiation Therapy).

**Fig. 2 Fig2:**
[figure not shown]
The experimental and control group clinical target volume setting (red line): **A** The clinical target volume setting of the experimental group was as follows: vertebral and adjacent tissue destruction according to the International Spine Radiosurgery Consortium consensus guidelines that recommend that the vertebral body is divided into six parts. **B** The clinical target volume setting of the control group: the entire vertebra that has been destroyed

Before starting treatment, the qualified recruitment participants will explain the common ethical issues, objectives, design, description, implementation, requirements and schedule of this study to every potential study participant.

### Objectives

The primary endpoint is pain relief rate. The secondary endpoints are the incidence and types of side effects.

### Inclusion criteria

Aged 18-80 yearsPatients with vertebral metastasis of solid tumors confirmed by pathology and imaging, and a number of discontinuous vertebral metastases ≤ 3, who had no tumor tissue compressing the spinal cordECOG0-1No serious chronic diseases, such as severe hypertension, diabetes or heart diseaseThere was no contraindication to radiotherapy and no previous radiotherapy targeting a vertebral metastasisEstimated survival time ≥ 3 monthsThe patient or their family members sign the informed consent form and were willing to cooperate with the follow-up

### Exclusion criteria

Bone destruction in benign diseases and diffuse bone destruction, such as multiple myeloma, lymphoma, or leukemia with bone marrow infiltrationParticipated in other clinical trials of drug or physical therapy for target lesions in the past four weeksUncontrolled and/or severe disease, including:Myocardial infarction or myocardial ischemia and arrhythmia (≥ 2 levels of congestive heart failure according to the NYHA and QTc ≥ 480 ms)≥ CTCA Elevel 2 infection or long-term unhealed woundActive bleeding due to dysfunctional coagulationSystolic blood pressure greater than or equal to 180 mmHg and diastolic blood pressure greater than or equal to 110 mmHgAccording to the judgment of the researchers, the tumor invaded the large blood vessels and likely caused fatal bleeding during the treatmentThose who had a history of drug abuse and were unable to quit, or had mental disordersHad received surgery or radiotherapy for the target lesion in the past six monthsThe researcher judged that there were serious accompanying diseases that would endanger the safety of patients or affect the completion of the study.

### Drop-out criteria

The withdrawal of the informed consent of patients.A decision by the researchers to discontinue the study to ensure patients’ safetyA decision by the researchers or patients to stop the research in case of toxic side effectsResearchers’ judgment

### Radiotherapy

Before radiotherapy, all patients received computed tomography (CT) scans with a thickness of 3 to 5 mm. These CT scans were used to contour the gross tumor volume (GTV), clinical target volume (CTV) and organs at risk (OARs). The GTV was profiled according to CT scans, MRI and ECT. The clinical target volumes include the area of vertebral destruction and adjacent parts (study group) or the whole vertebral body (control group). The planning target volume (PTV) include organ movement and a daily setting error of 0.3 cm based on the CTV. Radiotherapy will be performed as IGRT, which will be administered using a line accelerator (energy = 6MV) in 10fractions (3 Gy/ fractionation, once a day from Monday to Friday).

### Data collection and management

This study will collect the patient’s name, age, gender, diagnosis of primary tumor, location and number of vertebral metastases, pain score and imaging findings. The above information will be recorded in a unique case report for each patient. These data will be input and saved in the electronic data management system established by Mianyang Central Hospital. The final data will be reviewed, locked and used for final data analysis by key researchers and statistical analysts.

### Measurement of the primary and secondary endpoints

Pain relief will be assessed by patients using the numerical rating scale before radiotherapy, two weeks, three months, six months and every six months after radiotherapy. The pain relief rate is the primary endpoint of this study. The secondary endpoint was a follow-up on the occurrence of side effects and the positive results of imaging, such as radiation spinal cord injury and pathological fracture. The vertebral bodies will be scanned with CT to identify radiogenic injury of the spinal cord and vertebral compression fracture.

Adverse events are being recorded in accordance with the requirements of the MedDRA. The classification of side effects was based on the CTCAE of National Cancer Institute.

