### Statistical analysis and randomization

We estimated the sample size based on paper of Fleiss, JL et al. [7]. We performed non-inferiority and equivalence trials with α = 0.025, 1-β = 0.8 and non-inferiority *Δ* = -0.15 using Pearson*X*^2^test, power = 0.809, *H*0: πt—πc ≤ -0.15, *H*1: πt—πc > -0.15.We estimate a loss to follow-up rate of 10% and the resultant required number of patients was 66. The rate of pain relief in patients with vertebral metastases receiving radiotherapy will be measured according to the results of previous trials including that by Howell et al. [8]. Randomization will be administered centrally by the SPSS24.0 software at Mianyang central hospital. Patients who meet the inclusion criteria will be randomized on a1:1 basis to one of the 2 groups. The randomization will conduct by Mianyang Central Hospital through spss24.0 software. Patients who meet the enrollment conditions will enter the control group and the study group in a ratio of 1:1.

The number, proportion and 95% confidence interval of patients with pain relief will be reported. The related toxicity will analyze by Fisher exact test.

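### CT of the vertebral bodies is the scan named to identify radiation spinal cord injury, but a negative CT cannot support a statement that cord injury was absent in either arm

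*Protocol article*

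**What the plan says.** The section on measurement of the primary and secondary endpoints describes the secondary endpoint in two parts: the occurrence of side effects, and "the positive results of imaging, such as radiation spinal cord injury and pathological fracture". It then names the scan: "The vertebral bodies will be scanned with CT to identify radiogenic injury of the spinal cord and vertebral compression fracture". One test is thus assigned to two outcomes, one in bone and one in the cord.

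The same section gives a second, clinical route. Adverse events are recorded to MedDRA requirements, and "The classification of side effects was based on the CTCAE of National Cancer Institute".

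MRI is mentioned once, in the Radiotherapy section, for contouring before treatment: "The GTV was profiled according to CT scans, MRI and ECT". The article names no follow-up MRI and no neurological assessment for cord injury. The Data collection section lists the pain score and imaging findings but not neurological status.

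The Background names cord injury among the harms of interest: "We also investigated if side effects such as twinkling bone pain, spinal cord radiation injury, vertebral compression fracture, and nerve root compression were reduced". For the comparison, the statistical section says "The related toxicity will analyze by Fisher exact test".

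**The concern.** This is a stated measurement rule, not a detail left to another document. As printed, an outcome inside the spinal cord is to be identified by a scan of the surrounding bone. If that scan is clear, the natural table entry is zero cord injuries in both arms, and the natural sentence is that neither target volume injured the cord. The scan cannot carry that sentence.

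The sentence would matter because sparing the cord is part of the rationale for the smaller target. The Discussion argues that a reduced target avoids excess irradiation of nerve and spinal cord. It adds that, if pain relief proves equivalent, the next step is a higher dose to the reduced target. Cord-safety results from this trial would be a natural input to that step.

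**Working it through.** No figure in the article is contested, so there is none to reproduce. The check has two parts.

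**1. The statements side by side**

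| Outcome | Imaging route in follow-up | Clinical route |
|---|---|---|
| Vertebral compression fracture | CT of the vertebral bodies (suitable) | CTCAE-graded adverse event |
| Radiation spinal cord injury | CT of the vertebral bodies (not reliable for this) | CTCAE-graded adverse event |

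For cord injury, the imaging route is the weak one and the clinical route is sound for symptomatic cases. The article does not say which route defines a case, or what a negative CT means when no symptoms are recorded.

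**2. What imperfect detection does at this sample size (illustration)**

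Inputs from the statistical section: "We estimate a loss to follow-up rate of 10% and the resultant required number of patients was 66", with 1:1 allocation, so 66 / 2 = 33 per arm. Assumed, because the article gives no values: true rates of 10% in the control arm and 0% in the study arm; CT sensitivity s of 100%, 50% or 20%; and a fraction c of cases recorded clinically whatever CT shows. Fisher's test is taken as two-sided at 0.05.

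Expected control cases recorded = 33 × 0.10 × [c + (1 − c) × s].
Chance of no case in either arm = (1 − 0.10 × [c + (1 − c) × s])^33, because the study arm contributes none.

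| c | s | Recorded fraction | Expected cases | Chance of none |
|---|---|---|---|---|
| 0 | 100% | 1.00 | 3.3 | 0.90^33 = 3% |
| 0 | 50% | 0.50 | 1.65 | 0.95^33 = 18% |
| 0 | 20% | 0.20 | 0.66 | 0.98^33 = 51% |
| 0.5 | 50% | 0.75 | 2.48 | 0.925^33 = 8% |
| 0.5 | 20% | 0.60 | 1.98 | 0.94^33 = 13% |
| 1 | any | 1.00 | 3.3 | 0.90^33 = 3% |

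The rows with c = 0 treat CT as the only way to find a case. The last row is the case where every injury is symptomatic and recorded, and the choice of scan then makes no difference. The article does not place the trial between these limits.

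**Significance**

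With 33 per arm, two-sided Fisher p-values are:
- 2 v 0: 2 × (33 × 32) / (66 × 65) = 0.49
- 5 v 0: 0.053
- 6 v 0: 0.024

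Under 10% v 0%, power is the chance of at least 6 control cases. That is 10.6% with every case detected and 0.5% if half are detected. At a true control rate of 1%, only 33 × 0.01 = 0.33 cases are expected and power is about 0% by any method. Allowing for the 10% loss (66 × 0.9 = 59.4, about 30 per arm) gives 7.3% in place of 10.6%, and 6 v 0 is still needed (p = 0.024).

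**The case against.** The strongest reply is that CT is not the only route. Side effects are collected and graded by CTCAE alongside imaging, and nothing in the text makes CT the sole test or says that a clear CT records absence. This stands. A reader might infer that cord injury as a whole will be under-counted in both arms in proportion to CT's sensitivity. The documents do not support that: the proportion would apply only to cases not already recorded clinically, and neither the sensitivity nor the share of such cases is given.

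A second reply is that the trial's conclusions would hardly change. This also stands for hypothesis testing. Even 2 v 0 with perfect detection is far from significant, and the primary endpoint, margin and sample size are untouched. A reader might also infer a bias favouring one arm. The same scan is used in both arms, so what is lost is cases, not balance.

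A third reply is that a clinical definition does not recover the asymptomatic cases that CT would miss. This is correct. The fix aligns the claim with what is measured; it does not find more cases.

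A fourth reply is that a condensed article leaves diagnostic detail to the full protocol. That would answer a complaint about missing detail. Here the article states which scan identifies the injury, and that statement is what needs correcting.

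**Conclusion.** The point holds in limited form. The article makes radiation spinal cord injury an imaging-positive secondary outcome and names for it a scan that does not reliably show damage within the cord. A negative CT therefore cannot support a statement that cord injury was absent in either arm. The weakness lies in the imaging-defined endpoint and the safety wording built on it, not in the capture of symptomatic injury.

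The size cannot be derived from the article. Under the assumed 10% v 0%, the chance of recording no case at all ranges from 3% (full detection) to 51% (20% sensitivity and no clinical capture). If the true rate is near 1%, the numerical effect in 66 patients is very small. A significant difference between arms is unlikely whichever method is used.

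The conclusion rests on one premise from outside the document, that CT shows intrinsic cord damage poorly. This is general imaging knowledge and needs no particular source or figure. The change is worth making because it is cheap and prevents a falsely reassuring sentence, but it does not threaten the primary analysis.

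**What to change.** In the section on measurement of endpoints:

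- Limit the CT sentence to vertebral compression fracture.
- Define the cord-injury endpoint by CTCAE-graded neurological adverse events, collected at the follow-up visits already scheduled (two weeks, three months, six months, then every six months). Use MRI findings where MRI is done for new signs. No scheduled MRI is added.
- State that a negative CT will not be reported as absence of cord injury.

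Fisher's exact test can stay as planned, with the counts per arm shown.

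Cost: revised endpoint wording and a short neurological symptom item at each visit. The listed visits are described only as time points for the patient-rated pain scale, so the item is a real, though small, addition. Asymptomatic cord injury will not be counted, and the report should say so.

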### Statistical analysis and randomization

We estimated the sample size based on paper of Fleiss, JL et al. [7]. We performed non-inferiority and equivalence trials with α = 0.025, 1-β = 0.8 and non-inferiority *Δ* = -0.15 using Pearson*X*^2^test, power = 0.809, *H*0: πt—πc ≤ -0.15, *H*1: πt—πc > -0.15.We estimate a loss to follow-up rate of 10% and the resultant required number of patients was 66. The rate of pain relief in patients with vertebral metastases receiving radiotherapy will be measured according to the results of previous trials including that by Howell et al. [8]. Randomization will be administered centrally by the SPSS24.0 software at Mianyang central hospital. Patients who meet the inclusion criteria will be randomized on a1:1 basis to one of the 2 groups. The randomization will conduct by Mianyang Central Hospital through spss24.0 software. Patients who meet the enrollment conditions will enter the control group and the study group in a ratio of 1:1.

The number, proportion and 95% confidence interval of patients with pain relief will be reported. The related toxicity will analyze by Fisher exact test.

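### The drop-out criteria let researchers take a patient out of the research, not only off treatment, so avoidable and possibly unequal loss of pain scores can move the non-inferiority result in either direction

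*Protocol article*

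**What the plan says.** The Drop-out criteria section lists four grounds: the patient withdraws consent; researchers discontinue for safety; researchers or the patient stop because of toxicity; and the researchers' judgment, with no further condition. Researchers can act on three of the four. The safety and toxicity grounds are worded as ending the study or the research, not as ending radiotherapy. Nothing in the section says that pain scoring or toxicity assessment continues afterwards.

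On the endpoint, Measurement of the primary and secondary endpoints states: "The pain relief rate is the primary endpoint of this study". Scores are due before radiotherapy and then at "two weeks, three months, six months and every six months after radiotherapy". Side effects are the secondary endpoint, and the abstract expects fewer of them with local irradiation.

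Statistical analysis and randomization sets a non-inferiority margin of -0.15 on the difference in relief rates, with "α = 0.025, 1-β = 0.8" and patients "randomized on a1:1 basis to one of the 2 groups". On losses it says: "We estimate a loss to follow-up rate of 10% and the resultant required number of patients was 66". On analysis it says: "The number, proportion and 95% confidence interval of patients with pain relief will be reported". The article does not state the denominator of that proportion.

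**The concern.** A drop-out rule governs what staff do during the trial. An analysis plan can choose a denominator later, but it cannot recover a pain score that was never taken because the patient had been removed from the research.

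Two features make such losses potentially informative here. First, toxicity is both a reason for leaving and an outcome on which the arms are expected to differ. Second, the article describes no blinding, and the team that contours the target volume must know the arm. An open-ended discretionary ground could therefore be used differently in the two arms, even without intent.

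In a non-inferiority comparison with a 15-point margin and 66 patients, a few non-responders missing from one arm change the estimated difference by an amount that matters against the margin. The same rule also cuts short the recording of side effects, the secondary endpoint, in the patients who had them.

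**Working it through.** **Inputs from the article.** Margin 0.15, α = 0.025 (read as one-sided, because the hypotheses are one-sided), 66 patients allocated 1:1, so 33 per arm, and a loss allowance of 10%. Expected number lost: 66 × 0.10 = 6.6, so 6 or 7 patients.

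**The plan's own figure.** The 66 cannot be reproduced, because no relief rate is stated; the rates are only referred to, as something that "will be measured according to the results of previous trials". That is a separate matter. It means the relief rates below are assumptions.

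**Assumptions.** Control (whole-vertebra) relief πc = 0.60, 0.70 or 0.80; local relief πt = πc - 0.15, the boundary of the null hypothesis; every lost patient is a non-responder and is left out of the denominator; non-inferiority is declared if the lower limit of a Newcombe 95% interval for the difference exceeds -0.15.

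**Step 1: direction, on expected counts at πc = 0.70.** Expected responders are 0.55 × 33 = 18.15 (local) and 0.70 × 33 = 23.1 (whole vertebra). The true difference is -0.150.

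| Lost, local v whole | Local rate | Whole rate | Difference |
|---|---|---|---|
| 5 v 2 | 18.15/28 = 0.648 | 23.1/31 = 0.745 | -0.097 |
| 3 v 3 | 18.15/30 = 0.605 | 23.1/30 = 0.770 | -0.165 |
| 2 v 5 | 18.15/31 = 0.585 | 23.1/28 = 0.825 | -0.240 |

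The sign of the shift depends on which arm loses more.

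**Step 2: false non-inferiority rate.** The lower limit is L = d - √[(pt - lt)² + (uc - pc)²], where d = pt - pc and lt and uc are the Wilson limits. The rate is the probability that L > -0.15, taken over two binomial counts of size 33 after removing the lost non-responders. It was obtained by simulation and checked by summing the exact binomial probabilities.

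| Lost, local v whole | πc = 0.60 | πc = 0.70 | πc = 0.80 |
|---|---|---|---|
| none | 0.03 | 0.03 | 0.03 |
| 5 v 2 | 0.07 | 0.10 | 0.15 |
| 3 v 3 | 0.03 | 0.03 | 0.04 |
| 2 v 5 | below 0.01 | below 0.01 | below 0.01 |

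**Step 3: a second method.** A simulation with a Wald lower limit and losses of 15% local and 5% whole-vertebra gave 8.1% (0.70 v 0.55) and 12.3% (0.80 v 0.65). Equal losses of 10% gave 2.3% (0.80 v 0.65). The pattern is the same.

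**The case against.** The strongest objection is that the article never says that patients who drop out are excluded. That is correct. A reader might infer from the 10% allowance that they are removed and not scored, but the sentence only sets the sample size, and trials that analyse every randomised patient also inflate for loss. The analysis set and the handling of missing scores are commonly left to the full protocol or the analysis plan, neither of which is shown, so their absence here is no finding.

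A reader might also count death as a drop-out path because entry requires an expected survival of at least three months. Death is not among the listed criteria, and three months is an entry minimum, not a typical survival. Nor is it established that patients leave before any pain score: one is due two weeks after radiotherapy, and the article does not fix which visit defines the primary endpoint.

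The direction of bias is open as well. If local irradiation is less toxic, as the trial expects, toxicity exits would be more frequent in the whole-vertebra arm, which makes non-inferiority harder to show. It is tempting to quote one-sided cases: with 3 or 6 local non-responders lost and none from control, the error is 0.07 to 0.11 or 0.14 to 0.32. The second puts about the whole 10% allowance into one arm, and nothing in the article supports that split.

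What survives these objections is the wording of the drop-out criteria. It is a rule stated in the article, and no analysis choice can undo the data loss it permits.

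**Conclusion.** The point holds as a defect in the drop-out rule. As written, it lets researchers end participation in the research on open-ended grounds, one of which is tied to an outcome expected to differ by arm, and it does not keep those patients in follow-up.

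The consequence is conditional. If scores are lost, the losses are unequal and related to non-response, and the patients are left out, then about 10% loss overall can move the false non-inferiority rate from about 0.03 to between 0.07 and 0.15 (5 local v 2 whole-vertebra) or to below 0.01 (2 v 5). Equal loss leaves it at about 0.03 to 0.04. These figures rest on assumed relief rates, splits and interval method. The documents do not support a claim that the error rate must rise. The point is worth correcting because the correction is cheap and lost scores cannot be recovered.

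**What to change.** Reword the Drop-out criteria section so that:

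- only withdrawal of consent ends follow-up;
- a decision on safety, toxicity or researcher judgment may end study treatment, but the patient keeps the scheduled pain scores and toxicity assessments;
- such a patient stays in the randomised arm for the pain relief rate;
- the reason for stopping treatment is recorded.

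This leaves unchanged when treatment may be stopped. The scoring of patients who still have no pain score, and any sensitivity checks, belong in the analysis plan. They need thought there, because counting all such losses as failures would itself cost power at 66 patients.

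The cost is a wording amendment and a few extra follow-up contacts. The pain score is the patient's own rating on a numerical scale and is already scheduled.

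### The stated power of 0.809 for 66 patients does not hold if both volumes relieve pain equally: it is about 0.21 to 0.31 at assumed common relief rates of 50% to 80%, and 0.809 needs about 95.6% in both arms or an unstated study-arm advantage

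*Protocol article*

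**What the plan says.** The section Statistical analysis and randomization gives the design: "We performed non-inferiority and equivalence trials with α = 0.025, 1-β = 0.8", with "non-inferiority *Δ* = -0.15", a one-sided alternative that the study-minus-control difference exceeds -0.15, and an achieved power of 0.809. The authors "estimate a loss to follow-up rate of 10% and the resultant required number of patients was 66". Allocation is 1:1. The Abstract (Methods) shows that 66 is the total over both arms: "Sixty-six patients with pain caused by vertebral metastasis were randomly divided into two groups".

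On the relief rate the section says only this: "The rate of pain relief in patients with vertebral metastases receiving radiotherapy will be measured according to the results of previous trials". It gives no rate for either arm and no assumed true difference.

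On what is expected, the Abstract (Methods) sets out to verify whether "reducing the radiotherapy range for vertebral metastases can achieve the same effect as whole vertebral radiotherapy while minimizing side effects". The last paragraph of the Discussion makes the next step, dose escalation, depend on showing that local and whole-vertebra irradiation are equivalent for pain relief. Both arms receive the same dose.

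**The concern.** The power of a non-inferiority test on two proportions depends on the true rate in each arm. With about 30 patients per arm and a margin of 15 points, 0.809 looks far too high if the arms are equal and the relief rate is moderate, because the standard error of the difference is then about 0.10 to 0.13.

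The stake is how the result is read. A reader told that power is 0.81 will take a missed margin as a sign that local irradiation is worse. If power is really 0.2 to 0.3, a missed margin is the expected outcome even when the two volumes work equally well.

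**Working it through.** **Inputs from the document.** Margin 0.15; alpha 0.025, taken as one-sided because the hypotheses are one-sided (z = 1.96); 66 randomized in total, 1:1; 10% loss. The loss step is consistent: 66 × 0.9 = 59.4 and 60 × 1.1 = 66, so about 30 evaluable per arm.

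**Input not in the document.** The relief rates. I assume a common rate p and show 50% to 95%.

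**Formula (unpooled normal approximation).** Power = Φ[(pt − pc + 0.15)/SE − 1.96], with SE = √[(pt(1−pt) + pc(1−pc))/30]. With equal rates, SE = √[2p(1−p)/30].

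**Step 1: what reproduces 0.809.** Since Φ(0.874) = 0.809, the ratio (difference + 0.15)/SE must be 1.96 + 0.874 = 2.834.
- Equal rates: SE must be 0.15/2.834 = 0.053, so p(1−p) = 30 × 0.053²/2 ≈ 0.042 and p ≈ 0.956.
- Control 75%, study 88%: 0.28/0.0988 = 2.833, power 0.809.
- Control 92%, study 95%: 0.18/0.0635 = 2.833, power 0.809.
- Pooled null variance, control 62%, study 80%: mean rate 0.71, SE0 = √(2 × 0.71 × 0.29/30) = 0.1172, SE1 = √[(0.62 × 0.38 + 0.80 × 0.20)/30] = 0.1148. Power = Φ[(0.33 − 1.96 × 0.1172)/0.1148] = Φ(0.874) = 0.809.

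These unequal pairs are examples. They are not the authors' recovered inputs.

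**Step 2: power at zero difference, 30 per arm.**

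| Common rate | SE | 0.15/SE − 1.96 | Power |
|---|---|---|---|
| 50% | 0.1291 | −0.80 | 0.21 |
| 60% | 0.1265 | −0.77 | 0.22 |
| 70% | 0.1183 | −0.69 | 0.24 |
| 80% | 0.1033 | −0.51 | 0.31 |
| 90% | 0.0775 | −0.02 | 0.49 |
| 95% | 0.0563 | 0.71 | 0.76 |

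**Step 3: do other readings rescue the figure at 50% to 80%?**
- No loss at all (33 per arm): 0.23 to 0.33.
- Exact binomial power at 30 per arm: 0.21 to 0.34 (Wald test), 0.23 to 0.29 (score test).
- One-sided alpha 0.05: 0.32 to 0.42.
- 60 or 66 read as the number per arm: 0.38 to 0.58.

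None comes near 0.809.

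**Step 4: precision.** The Wald 95% half-width is 1.96 × SE: 0.253 at 50%, 0.248 at 60%, 0.232 at 70%, 0.202 at 80%. With 21/30 relieved in both arms the interval is −0.23 to +0.23, so identical observed results miss the −0.15 margin. At 27/30 in both arms the half-width is 0.152, which still misses; at 28/30 it is 0.126, which passes.

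**The case against.** The strongest reply is that the article states no relief rates, so 0.809 cannot be shown to be miscalculated. A full protocol may hold the rates, and the article points to a cited earlier trial for them. This stands: a reader might infer an arithmetic error, and the document does not support that. The absence of the rates from an article is also not the point by itself. The point survives because no undisclosed pair of rates can give 0.809 at this size with equal arms unless relief is near 96%.

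A second reply is that non-inferiority may be planned on a true advantage. The alternative hypothesis allows one, and so does the expectation in the Abstract's Discussion that local irradiation will do no worse. This also stands, so it would be too strong to say that an assumed advantage contradicts the aim. It does sit badly with the same-effect wording of the Abstract (Methods) and the equivalence sought in the Discussion. Nothing in the article predicts better pain relief from the smaller volume at the same dose.

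A third reply is that relief could be very high. The Background remarks that the effect varies among patients, but that does not exclude a high proportion of responders, and the article as shown sets no threshold for relief that would bound the rate. At 92% against 95% the advantage needed is only 3 points. The low power therefore depends on the assumed range and is not proven for this population.

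Finally, a reader might take 62% against 80% as the planning assumption because it returns 0.809. The match depends on the formula and on exactly 30 per arm: the unpooled formula gives 75/88 and 92/95, and the pooled formula at 29 per arm gives 56/76.

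**Conclusion.** The point holds as a statement about a power figure that the design does not have under equal efficacy at relief rates below about 95%. Across assumed common rates of 50% to 80%, power is 0.21 to 0.31. If the volumes truly are equal, the trial would then miss its margin in about 69% to 79% of repetitions (1 − 0.31 to 1 − 0.21). At 90% the power is 0.49, at 95% it is 0.76, and it reaches 0.809 at about 95.6%.

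This rests on 30 evaluable patients per arm, one-sided alpha 0.025, the normal approximation and a zero true difference. The relief rates are assumptions, because the document gives none. The finding does not show that the authors miscalculated, which rates they used, or that the trial must fail.

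**What to change.** In Statistical analysis and randomization:

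1. State the assumed relief rate in each arm and the assumed true difference.
2. Replace the power of 0.809 with the power that 66 patients give at zero difference (for example 0.24 at 70% or 0.31 at 80%, with 60 evaluable). Otherwise say explicitly that 0.809 is conditional on a named study-arm advantage or on a near-ceiling rate in both arms.
3. State the expected precision: a Wald 95% half-width of about 0.20 to 0.25 for the difference at rates of 50% to 80%, for example ±0.23 with 21/30 relieved in both arms.
4. Say that missing the margin is inconclusive and is not evidence that local irradiation is inferior.

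The cost is the rewording of one paragraph and a less favourable stated power. No added patients are required, and nothing in treatment or follow-up changes.
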